#### Target population (mother-infant dyads)

Evaluation of the intervention outcomes will target mother-infant dyads who are admitted to rooming-in programs at one of the eight participating hospitals in Alberta. Eligibility of a mother-infant dyad to participate in the rooming-in model of care implemented by the NASCENT study/ project will be coordinated by each of the sites according to the following criteria:
*Inclusion criteria*: Infants born at greater than 36 weeks’ gestation and a weight of greater than 2000 g born to mothers who report opioid use during pregnancy. Infants at risk for NAS must be well enough to participate in the rooming-in model of care.
*Exclusion criteria:* Infants born at less than 36 weeks and/or birth weight less than 2000 g. Infants with congenital anomalies will be excluded because at most sites these infants would be admitted to NICU.

The goal is for site champions and study team members to recruit participants prior to hospital admission for delivery, but potential participants will also be approached if their delivery presentation is the first recruitment opportunity. During pregnancy, mothers who wish to participate in rooming-in will be identified through colleagues at community organizations. Consent to participate in the study (*i.e.,* consent to extract data using healthcare number and 6-month follow up)may be obtained prior to or immediately after delivery at the hospital.

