**Methods:**

A stepped wedge cluster randomized trial will be used to evaluate the implementation of an evidence-based rooming-in approach in the postpartum period for infants born to mothers who report opioid use during pregnancy. Baseline data will be collected and compared to post-implementation data. Six-month assessment of maternal and child health and an economic evaluation of cost savings will be conducted. Additionally, barriers and facilitators of the rooming-in model of care within the unique context of each site and across sites will be explored pre-, during, and post-implementation using theory-informed surveys, interviews, and focus groups with care teams and parents. A formative evaluation will examine the complex contextual factors and conditions that influence readiness and sustainability and inform the design of tailored interventions to facilitate capacity building for effective implementation.

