### Data collection and management

Prospective data collection will be developed in consultation with experts from existing NAS programs and informed by the Minimum Dataset for NAS registry recommendations [56]. Anonymous LOS data will be collected from administrative data for NAS admissions at all sites pre-initiation and at each implementation phase for patients that are not consenting participants in the study. Standardized forms will be used to collect data, including LOS, for consenting participants at discharge and at 6 months follow-up (Table 1 ).

**Table 1 Tab1:** Data collection: rooming-in intervention economic evaluation, and short-term social, health, and developmental outcomes

All sites	Number of Mother &Infant Dyads	Months Collected	Data
**Baseline data** (Anonymous) Throughout all phases	160–240	6 – 27	LOS in NICU, pharmacological management, breastfeeding at discharge and apprehension rates
**During implementation-** (consenting participants at/before discharge)	Up to 240	9 – 30	LOS, Perinatal characteristics, NAS pharmacologic management, rates of breastfeeding, maternal participation in ODP/VODP, child apprehension
**After discharge** (consenting participants at 6 months)	Up to 240	24	Maternal: participation in ODP/VODP, breastfeeding duration, involvement with Children’s Services, maternal depression (Edinburgh), parenting self-efficacy, quality of life Baby: NAS pharmacologic management, short-term developmental assessment using the Ages and Stages Questionnaire: SE-2 and ASQ 3

De-identified data will be collected and managed using REDCap electronic data capture tools hosted at The University of Alberta [57, 58]. REDCap (Research Electronic Data Capture) is a secure, web-based software platform designed to support data capture for research studies. In addition to chart review, provincial and national health related databases will be used to collect baseline LOS, perinatal characteristics, and data to inform the economic analysis. Data linkage will be through unique identifiers and probabilistic linkage. Data collection will be coordinated by site champions and the NASCENT study investigators. Confidentiality will be maintained throughout the study. Only study investigators will have access to the final dataset.

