**Fig. 3 Fig3:**
[figure not shown]
Partnerships are crucial for the continuum of care

To facilitate user and stakeholder engagement, NASCENT will support identifying and connecting with relevant stakeholders for each site; assist in forming relationships with province-wide services, programs and leaders, and practitioners; conduct preliminary meetings with relevant stakeholders to inform the upcoming program; and form spaces for collaboration and continuum of care (*i.e.*, facilitating referral pathways to hospitals that provide rooming-in care and safe transitions to the community after discharge). Moreover, stakeholders will be involved in the development of educational material to promote culturally safe, trauma-informed patient-centered care and the design of evaluation questions, analysis, and interventions.

With each step (3-month period) in the trial, data will be collected as outlined above. These data will be shared with stakeholders in feedback sessions. Specifically, information related to baseline and current rates of admission for NAS, number of participants, participation rates, LOS, and consistency of care implemented during the intervention will be fed back to sites and shared with funders. Process data related to expected implementation timeline and completion of staff training will also be collected and shared. Prospective data collection and frequent analysis (every 3 months) for each site and for the study’s overall including changes to the original plans will allow the NASCENT team to closely monitor if outcome measures are aligning with the improvement forecast. This will allow the team to regularly report actual performance metrics back to partners and funders. The study leadership team, clinicaltrials.gov, REBs, and funders will be notified of any protocol modifications. Adverse events and other unintended events potentially related to the rooming in care will be reviewed by the site implementation team and the study leadership team and reported to relevant REBs.

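### As written, intervention outcomes come from dyads who entered rooming-in and control LOS from NAS admissions with no matching criteria, so the primary contrast could favour rooming-in without a true effect

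*Protocol article*

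**What the plan says.** Only the protocol article is at hand. It randomises eight hospitals to the order in which they start rooming-in (Aim 1: design). On who supplies the outcome data, it says the following.

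- **Intervention side** (Target population): "Evaluation of the intervention outcomes will target mother-infant dyads who are admitted to rooming-in programs". Mothers report opioid use and, where identified in pregnancy, wish to take part. A clinical condition is added: "Infants at risk for NAS must be well enough to participate in the rooming-in model of care". One exclusion is justified by NICU use itself: "Infants with congenital anomalies will be excluded because at most sites these infants would be admitted to NICU".
- **Control side** (Data collection and management): "Anonymous LOS data will be collected from administrative data for NAS admissions at all sites pre-initiation". The section does not say that the gestation, weight, anomaly or fitness criteria are applied to these records.
- **After rollout** (same section): anonymous LOS continues "at each implementation phase for patients that are not consenting participants in the study". Table 1 puts these records in the row headed baseline data, marked "Anonymous) Throughout all phases". The implementation row holds consenting participants.
- **Comparison** (Abstract, Methods): "Baseline data will be collected and compared to post-implementation data".
- **Analysis** (Statistical Analysis): mixed models and estimating equations are named, and infants never admitted to NICU count as 0 days. No analysis set is named, and nothing says that infants are analysed by their site's condition in the period.

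**The concern.** Randomising the rollout order protects a comparison of all eligible infants at a site before and after its start. It does not protect a comparison in which one side is filtered after the start.

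Three of the filters (the mother's willingness, the judgement that the infant is fit, and actual admission to rooming-in) exist only once a site has crossed over. No control-period record can show who would have passed them. They are also closely tied to the outcome: rooming-in is the alternative to NICU, and the outcome is NICU days. Infants too unwell to room in, or whose mothers decline, would leave the intervention mean while their counterparts stay in the control mean. Site effects and period adjustment cannot remove this, because the selection happens within site-periods.

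The Table 1 label could add to the problem. If post-rollout non-participants are analysed as baseline, and if they stay longer, they raise the control mean as well. At stake is whether the primary estimate is a randomised comparison.

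**Working it through.** **Inputs from the article**
- Mean NICU LOS 15 days, SD 3, ICC 0.1, 8 sites, target 2.75 days (Sample size/feasibility). Mean 14 days among admitted infants (The setting).
- 75% of infants with NAS go to NICU (The setting; Sample size/feasibility). The rest count as 0 days.
- 70% maternal participation; 75% of participating dyads expected to join the research (Sample size/feasibility).

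**The plan's own figure.** 2.75/15 = 18.3%, which the article gives as 19% (19% of 15 would be 2.85 days). A standard stepped-wedge calculation (random site effect, fixed periods, 9 to 12 periods) gives power of 0.79 to 0.80 with one infant per site-period and above 0.99 with the planned 4 to 6. The stated power of at least 80% is therefore not in dispute, and 2.75 days serves as the yardstick below.

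**Difference expected with no treatment effect**

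*A. Participation unrelated to severity, same denominator on both sides.* The selected mean equals the overall mean, so the difference is 0 days.

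*B. Same denominator with 0-day stays on both sides, and exactly the mildest 70% participate.*
- Overall mean: 0.75 × 15 = 11.25 days.
- The mildest 70% are the 25% at zero plus 45% of all infants, which is the lowest 0.45/0.75 = 60% of those admitted.
- With a normal LOS of mean 15 and SD 3, the lowest 60% average 13.07 days.
- Selected mean: (0.45/0.70) × 13.07 = 8.40. Difference: 11.25 − 8.40 = 2.85 days.
- With a mean of 14: 10.50 − 7.76 = 2.74 days.

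This is perfect sorting by LOS, so it is the upper bound for a 70% share of this pool.

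*C. Controls are NICU admissions only, and 0-day stays enter the intervention side alone.* 15 − 11.25 = 3.75 days, or 14 − 10.50 = 3.50 days.

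**How strong must selection be?** If a share s is selected, the spurious difference is (1 − s) × (mean LOS of unselected − mean LOS of selected). To reach 2.75 days:
- s = 0.70 (participation): 2.75/0.30 = 9.2 days' gap.
- s = 0.70 × 0.75 = 0.525 (participating and consenting): 2.75/0.475 = 5.8 days' gap.

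**A narrower pool.** The article's participation estimate starts from NICU-admitted infants: 300 × 0.75 = 225, × 0.75 = 169, × 0.70 = 118 a year. If everyone in the pool has a NICU stay with SD 3, perfect selection of the shortest 70% shifts the mean by 1.5 days, short of the target. With a 70% share, selection alone reaches the region of 2.75 days only when 0-day stays are in the pool (B) or are treated differently on the two sides (C).

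**The case against.** The best reply is that the article also fits a whole-site comparison. Hospitals cross over in randomised steps with concurrent controls. Anonymous LOS is collected in every phase. Consent is tied to secondary outcomes and the 6-month follow-up. The economic analysis speaks of overall NICU bed use. The Target population section may mainly set eligibility for care, and an article often leaves the analysis set to the analysis plan. This stands as far as it goes: the data for a sound analysis are largely planned. It does not show that such an analysis is intended. The one sentence on whose outcomes are evaluated names rooming-in admissions, and Table 1 divides records by consent rather than by site condition.

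Four stronger readings are not supported.
- *That the trial would favour rooming-in even if nothing changed.* Scenario A gives 0 days, B is a perfect-sorting bound, and C requires controls restricted to NICU admissions. The article says only NAS admissions and does not limit the 0-day rule to one condition.
- *That 2.75 days is clearly exceeded.* B straddles it (2.74 to 2.85), and the narrower pool gives 1.5.
- *That no eligibility filter can be applied to controls.* Chart review and provincial and national databases are planned for baseline LOS and perinatal characteristics, so gestation, birth weight and anomalies could be matched. The gap is confined to willingness, fitness and rooming-in admission.
- *That mothers will move between hospitals and distort the comparison.* The article does mention "facilitating referral pathways to hospitals that provide rooming-in care", but in a passage on stakeholder engagement, and it lists no maternal residence data. No catchment analysis is asked for here.

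**Conclusion.** The point holds as a defect in what the article states. Followed literally, the intervention group is formed after crossover on factors that cannot be identified in control periods and that are closely tied to NICU days. The primary contrast could then favour rooming-in with no true effect.

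The size is unknown, because no LOS by participation is reported. The range is 0 days (selection unrelated to severity), about 2.7 to 2.9 days (perfect selection of the mildest 70%, 25% at zero, mean 14 to 15 days, SD 3) and 3.5 to 3.75 days (NICU-only controls, with zeros on the intervention side alone). These are assumption-based scenarios, not estimates. They matter because the upper two are about as large as the effect the trial is designed to detect. The article should be corrected before recruitment, which by its own trial status has not begun.

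**What to change.** State one primary analysis set in the Target population, Data collection and Statistical Analysis sections:

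- Include every infant at a site in a period who meets criteria ascertained the same way in both conditions: gestation, birth weight, no congenital anomaly, and an NAS or opioid-exposure code.
- Include them regardless of rooming-in admission, the judgement of fitness, or consent. Site eligibility for rooming-in care is not affected.
- Apply the 0-day rule in both conditions.
- Analyse by the site's randomised condition in that period. Anonymous records after rollout then count as intervention, and Table 1 should be relabelled accordingly.
- Report rooming-in participants as a secondary description.

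**Cost.** This is mainly wording, because LOS for non-consenting infants is already collected in all phases. The eligibility criteria must also be extracted for anonymous records, whose Table 1 row does not list them, from the chart review and databases already planned.

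The estimated effect will be smaller, because non-participants are included. As an illustration, suppose participants reach the pilot programme's 0.82 days and non-participants stay at 11.25. The participants-only contrast is 11.25 − 0.82 = 10.43 days. The hospital-level contrast is 11.25 − (0.70 × 0.82 + 0.30 × 11.25) = 7.30 days, still well above 2.75.

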The problem is a priority because of increasing prenatal opioid use and NAS in North America and in Alberta, Canada where this study is located [7, 8]. The human, societal, and economic impacts will continue to worsen if care practices remain unchanged. Pregnant women are a unique population. Societal norms task mothers with risk avoidance as a moral requirement, including the assumption that mothers will abstain from substance use during pregnancy; however, this cannot be enforced legally and also raises complex ethical questions about power and control of women’s bodies. These social norms contribute to social stigma, legal, and health responsibilities, which may lead pregnant women who use substances to hide their status [9, 10]. Substance use in pregnancy and resultant NAS is seen in all socio-economic strata and all racial and ethnic backgrounds. However, the consequences of that use, including legal, medical, and social, may be different due to discrimination [11]. There are also significant challenges and inequities related to which mothers are screened for opioid use during pregnancy, and hence when there may be involvement by Children’s Services, and potentially child apprehension [12, 13].

Furthermore, the economic impact of NAS is substantial. In the US in 2017 there were approximately 7.3 infants with NAS per 1,000 live births [14]. Infants receiving NAS pharmacological management had mean hospital charges of $93,400 (USD) and a mean length of stay (LOS) of 23 days [15]. Additionally, out of hospital and non-healthcare related costs of NAS are substantial. In particular, rates of child apprehension are high and there is often ongoing involvement with Children’s Services [4]. While data are not available for Alberta there are published data available for Manitoba (Canada) related to the cost of a child being in care. In the year 2016/2017 the Manitoba annual child welfare budget was $514 million or $46,800 per child in care [16].

There are tangible and intangible societal and economic benefits in maintaining and promoting intact mother-infant dyads. Child development and long-term mental and physical health outcomes are critically dependent on early establishment of a nurturing relationship between mothers and their infants [5]. This in turn contributes to healthier families, less dependence on social services, and improved future economic contributions to society.

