### The rooming-in model of care

*Rooming-in* is an evidence-informed model of care in managing NAS that is safe and effective [15, 17, 18] The focus is on keeping mothers and infants together throughout their hospital stay. With the rooming-in model of care, infants are cared for by their mothers in a supportive post-partum environment, avoiding the need for a long and expensive NICU admission. Mothers are provided with breastfeeding support; a standardized assessment of infant NAS symptoms by health care team members *e.g.*, *Eat, Sleep, Console (ESC)*(a tool designed to evaluate infants ability to manage withdrawal symptoms); with non-pharmacologic interventions, such as skin-to-skin care, and low stimulation environment [17–21]; ongoing social work support; an opportunity for maternal participation in an ODP; and supported transition home upon discharge in collaboration with community agencies. In addition, those involved in the provision of care to mothers and their infants with NAS receive education and support to address the stigma of drug use and its impact when caring for mothers with substance use disorder focusing on patient-centered and trauma-informed care [22, 23].

Another instrumental aspect of the rooming-in model’s long-term success is the continuum of care provided pre- and post-delivery, sometimes referred to as ‘*wraparound programs*’ [24]. Cross-sectoral collaborations that form connections between those involved with rooming-in in hospital settings and community support organizations/services is crucial to the continuum of care for mothers pre- and post-delivery [25].

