#### Target hospitals

The 8 sites participating in the study all have NICU and postpartum units and some have pediatric units as well (See Additional file 3 for the full list of participating sites). Each site serves different communities and has different care structures for labour and delivery and post-partum care. Sites have a range of experience with the rooming-in model of care, from no or limited (six sites) to several years of experience (two sites). The two sites with existing rooming-in models of care programs will continue to refine and enhance their approaches and support others as they start their implementation journey.

Participating sites will be supported by the NASCENT study through the implementation process in the following ways:Identification and formation of Site Implementation Teams: identification of site operational, medical, nursing, and social work champions and other key individuals that need to be involved from community agencies, public health units, amongst othersTraining and support of site championsIdentification of site-specific facilitators and barriersCreation of site-specific interventions and plan to prepare for NAS care, including identification of a dedicated space and commencement dates where rooming-in will take placeDevelopment of site-specific mechanisms to refer to an ODP/VODP programDevelopment of additional staff resources to address specific learning needsDevelopment of mechanisms for prenatal engagement of women who experience opioid dependency through community agencies and transition back to communityStaff education and training (as well as funding for educational time) led by the study Provincial Clinical Practice Lead

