### Mother-Infant dyad outcomes analysis

#### Statistical Analysis

NICU LOS was chosen as the primary outcome because NICU admission may occur for several medical reasons unrelated to NAS and a difference in LOS may be more meaningful in understanding NAS severity. Cases with no NICU admission will be assigned a NICU LOS of 0 days. Generalized Linear Mixed Models and Estimating Equations will be used in analyzing the primary and secondary outcomes: rates of pharmacological management of NAS, child apprehension, maternal participation in an ODP, maternal mental health, parenting self-efficacy, quality of life at discharge at 6 months follow up and, babies’ developmental outcomes at 6 months follow-up (see aim 1 above).

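### Intervention dyads enter by maternal report of opioid use but comparison infants come from administrative NAS admissions, so more mild, 0-day infants may be counted after rollout and lower mean NICU LOS without benefit

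*Protocol article*

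**What the plan says.** **Entry to the intervention.** Under Target population (mother-infant dyads), eligible infants are those "born to mothers who report opioid use during pregnancy", above stated gestation and weight limits, at risk for NAS and well enough to room in. No amount, duration or timing of use is set, and no NAS diagnosis is required. The same section says: "Evaluation of the intervention outcomes will target mother-infant dyads who are admitted to rooming-in programs".

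**Source of comparison data.** Data collection and management says: "Anonymous LOS data will be collected from administrative data for NAS admissions at all sites pre-initiation". The sentence extends this to each implementation phase for infants whose mothers are not consenting participants. Consenting participants' LOS is taken from standardized study forms.

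**Outcome rule.** Statistical Analysis says: "Cases with no NICU admission will be assigned a NICU LOS of 0 days".

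**Identification before rollout.** The Background describes stigma and legal consequences "which may lead pregnant women who use substances to hide their status". It also names "challenges and inequities related to which mothers are screened for opioid use during pregnancy".

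**Intervention components that bear on identification.** Under The rooming-in model of care, those providing care "receive education and support to address the stigma of drug use". Target hospitals lists "mechanisms for prenatal engagement of women who experience opioid dependency through community agencies". The NASCENT section has site champions working with community organizations to find and recruit participants. Table 4 adds education of pregnant women about rooming-in.

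**The concern.** The primary outcome is a mean per identified infant, so it depends on who is identified. The two conditions find infants by different routes: a mother's report on one side, an administrative NAS admission on the other. An exposed infant with little or no withdrawal can enter by the first route and be absent from the second.

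The intervention also acts on the first route. If stigma falls and community outreach works, more mothers should report use. Some of those added are likely to have infants who would have gone unnoticed before because they had few symptoms. Each such infant scores 0 days and pulls the mean down.

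A change that follows each site's own rollout is confounded with the treatment effect, and a calendar-time term cannot fully remove it. The rate of pharmacological management is exposed in the same way: 20% more infants, all untreated, would multiply any baseline rate by 1/1.2, a relative fall of 17%. The economic analysis also uses the decrease in LOS.

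**Working it through.** **Inputs from the article.** 244 affected newborns a year, 75% admitted to NICU, mean NICU LOS 14 days (The setting). Mean 15 days, SD 3, ICC 0.1, detectable difference 2.75 days, 8 sites, one site per step, 4 to 6 dyads per site per 3-month period (Sample size/feasibility). Pilot NICU LOS 10.33 to 0.82 days (NASCENT section).

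**Assumptions.** f, the fractional rise in identified infants, and L, their mean NICU LOS. The article gives neither.

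**Step 1. Whom the mean describes.** The setting equates a 2- to 3-week stay with 2,500 to 3,800 NICU days a year. 244 × 0.75 = 183 infants; 183 × 14 = 2,562 and 183 × 21 = 3,843. This agrees, so the stay is per admitted infant. With the others counted as 0, the mean over all identified infants is 0.75 × 15 = 11.25 days (0.75 × 14 = 10.5).

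**Step 2. Difference of source alone, disclosure unchanged.** The article does not say whether NAS admissions means NICU admissions or any hospital admission with NAS. If it meant NICU admissions only, the control mean would be 15. An intervention group in which 25% score 0 would have mean 11.25, a fall of 3.75 days (3.5 from 14) with no benefit. If it means any admission with NAS, this part is smaller. Exposed infants without a NAS record would then still enter on the intervention side only.

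**Step 3. Wider identification, no true effect.** New mean = (11.25 + f × L) / (1 + f).

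| Rise f | New mean, L = 0 | Fall | New mean, L = 3 | Fall |
|---|---|---|---|---|
| 10% | 10.23 | 1.02 | 10.50 | 0.75 |
| 20% | 9.38 | 1.88 | 9.88 | 1.38 |
| 30% | 8.65 | 2.60 | 9.35 | 1.90 |

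With L = 0, a fall of 2.75 days needs f = 11.25/8.50 − 1 = 0.32. From a baseline mean of 15 it needs 15/12.25 − 1 = 0.22.

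**Step 4. Would such a shift be declared significant?** I used the Hussey–Hughes variance with I = 8 sites, two baseline periods and T = 10 periods:

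Var = I·s²(s² + T·t²) / [(I·U − W)s² + (U² + I·T·U − T·W − I·V)t²]

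Here s² = SD²(1 − ICC)/n, t² = SD² × ICC, U = 36 intervention cells, and W = V = 204 (sums of squared period and site totals). The chance of rejection is Φ(shift/SE − 1.96), taking the whole shift to occur at crossover.

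- The plan's figure: the power statement gives no number of infants per site-period. With n = 4 to 6 and SD 3, SE is 0.535 to 0.444 and power for 2.75 days is at least 0.999, so the stated minimum of 80% is met.
- SD 3, mean 15: if added 0-day infants form 10% of the post-rollout sample (11 per 100 already identified), the shift is 1.5 days and the chance of rejection is 0.80 to 0.92.
- Counting zeros widens the SD to √(0.75 × 9 + 0.75 × 0.25 × 15²) = 7.0. With mean 11.25, SE is 1.249 to 1.036. A 10% share (1.125 days) gives 0.15 to 0.19; a 20% share (25 per 100; 2.25 days) gives 0.44 to 0.58.

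**Step 5. Against the pilot.** The pilot fall was 10.33 − 0.82 = 9.51 days. Falls of 1.02 and 2.60 days are 11% and 27% of that.

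**The case against.** The case on the other side has five parts.

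- **Nothing says that disclosure will rise, or that extra reporters are low-risk.** True; both are inferences. Eligibility also refers to infants at risk for NAS, and the prenatal engagement is aimed at opioid dependency, so outreach could add higher-risk dyads. A reader might infer that a mother with one brief early exposure qualifies on the same footing as any other, but the text does not go that far.
- **Timing.** A reader might infer an abrupt fall at crossover. Table 4 places community presentations at Baseline, and training and education of pregnant women at Pre-implementation. Part of any shift would then fall in control periods and blunt the contrast. Two sites already have several years of rooming-in, so a new rise there is less plausible. This stands, and it reduces the bias without removing it.
- **Size.** A reader might infer that the artefact could account for the whole result. Beside a fall like the pilot's it could inflate the effect but not create it. It matters most if the true effect is nearer 2.75 days.
- **Existing plans.** Economic analysis includes overall NICU bed use, a total to which 0-day infants add nothing, and admission and participation rates are fed back every 3 months. Neither is tied to the stepped wedge effect estimate.
- **Detail belongs in the analysis plan.** Case-mix sensitivity analyses often do. The two sources and the 0-day rule, however, are set in this article, and a common denominator has to be planned before data are drawn.

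**Conclusion.** The concern holds in this form. The article describes different ascertainment for intervention dyads and for control or non-participant infants, and it scores non-admitted infants as 0. Mean NICU LOS can therefore fall after rollout through a change in who is counted. The difference of source is in the text; the added effect of rising disclosure is a reasonable inference from the article's own account of hidden use and of the intervention.

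Under assumed rises of 10% to 30% in identified infants, the spurious fall is 1.0 to 2.6 days if they have 0 NICU days and 0.8 to 1.9 days if they average 3. These figures assume a baseline mean of 11.25 days, no true effect, and the whole shift falling after rollout.

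The documents do not show that maternal report is the wrong basis for offering rooming-in, that one criterion governs both conditions, or that the bias would explain a large effect. The point should be dealt with before recruitment, and the article gives the trial status as not yet recruiting.

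**What to change.** 1. Keep maternal report as the basis for offering rooming-in.
2. For the NICU LOS analysis, identify infants from the same administrative source and definition in control and intervention periods, whether or not they roomed in. State whether a NAS admission means a NICU admission or any hospital admission.
3. Add a supportive stepped wedge analysis of total NICU days among infants meeting the gestation and weight criteria with a NAS or opioid-exposure code, per 1,000 live births meeting the same criteria, by site and 3-month period. Coding may itself follow disclosure, but a newly coded 0-day infant adds nothing to the numerator, and one with NICU days counts against the intervention. This artefact therefore cannot produce a false benefit here.
4. Tabulate identified infants per 1,000 live births by site and period.
5. Read the per-infant result alongside items 3 and 4, but do not make agreement in direction a formal condition. Integrated knowledge translation plans referral pathways to rooming-in hospitals. Exposed women moving to those sites could raise NICU days per birth there and wrongly overrule a true effect.

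The cost is live-birth counts by site and quarter from the kind of administrative data already planned, one more model and one table. The per-birth measure is noisier than the per-infant mean and sensitive to referral between sites.
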